**Figure 1. Timeline - Recruitment to Completed eCRF**

[figure not shown]

#### 6.4 Withdrawal of individual subjects

Subjects can leave the study at any time for any reason if they wish to do so without any consequences. The investigator can decide to withdraw a subject from the study for urgent medical reasons.

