### 4.4 Sample size calculation

Superiority: In the control group we expect 40% antibiotic therapy in newborns at risk for EOS. To reduce this to 25% (reduction 15%) by use of the EOS calculator, (80% power, ICC 0,0025, alpha 0,05, 10 hospitals) a total sample size of 330 is required.

Non-inferiority: In the control group and the intervention group, we expect that 10% of newborn infants will fulfill one of the predefined safety criteria. The non-inferiority margin

is set at 15% (absolute difference 5%). The required sample size is 1640 (per cluster 164) (80% power, ICC 0,0025, alpha 0,025, 10 hospitals). Because both hypotheses regarding superiority (reduction in antibiotic therapy) and non-inferiority (adverse clinical outcome) have to be met, the study sample size equals the largest of the two sample sizes.

The potential drop-out or withdrawal is estimated at 10%. We will include 2x 915 newborn infants (total=1830), which means 183 per cluster. The analyses will be performed both according to the intention-to-treat (ITT) principle and according to a per-protocol (PP) analysis. All participants taking part in the study will be analyzed according to the ITT principle. Protocol deviations will be recorded and participants in whom major protocol deviations have occurred will be excluded from the PP analysis. These analyses will be both performed, since attending physicians are able to opt for clinical management not according to the advice of the assigned study protocol. This will be registered as a protocol violation in the eCRF, with accompanying justification (see chapter 3).

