## 6. METHODS

### 6.1 Study parameters/endpoints

#### 6.1.1 Main study parameter/endpoint

**Co-primary superiority outcome:** The proportion of patients that started antibiotic therapy for suspected and, or proven EOS in the first 24 hours after birth.

**Co-primary non-inferiority outcome:** A composite non-inferiority outcome regarding the presence of one or more of the following four predefined safety criteria, namely 1) the need for any respiratory support, and/or 2) the need for an intravascular fluid bolus for hemodynamic instability due to sepsis, and/or 3) referral to a Neonatal Intensive Care Unit for sepsis treatment, and/or 4) proven EOS.

- Respiratory support is defined as any form of respiratory support (invasive ventilation, continuous positive airway pressure (CPAP), high flow nasal cannula (HFNC), low flow oxygen) during the first week of life.
- Intravascular fluid bolus is defined as the intravenous administration of a fluid bolus of 10ml/kg within 15-30 minutes. It is the first step in the treatment of hemodynamically unstable newborns due to sepsis.
- Proven EOS is defined as a blood or cerebrospinal fluid (CSF) culture obtained within 72 hours after birth growing a pathogenic bacterial species.

The mentioned co-primary outcome criteria overlap with non EOS causes. For example, prematurity is also associated with the need for respiratory support or asphyxia with the need for intravascular fluid administration. It is for this that a randomization trial was chosen. We do not expect that a reduction in antibiotic exposure by using the EOS calculator will lead to significantly more of these outcomes. Because the trial is not blinded, there is a change that (unconscious) bias may occur. We expect that this will be limited by the cluster-randomized design on the one hand, and by the relatively objective criteria, on the other hand.

Furthermore, we decided for a composite non-inferiority outcome, based on four predefined criteria, since the incidence of each individual criterion is very low.

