## **6.2 Randomization, blinding and treatment allocation**

Randomization will take place at cluster level for either the EOS calculator or control (antibiotics administration according to NVK directive usual care). Centers will be randomized as clusters using a computer-generated algorithm. After randomization, the hospital will also switch to the protocol assigned after randomization (NVK guideline or EOS calculator use). This assigned protocol is standard care for newborns with suspected EOS during the study period in that hospital. This is independent of participating in this study (see chapter 3). Thus, hospitals nor physicians are blinded for the assigned study protocol. However, physicians may always opt for clinical management not according to the assigned study protocol.

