## **6.5 Replacement of individual subjects after withdrawal**

Subjects will not be replaced after withdrawal because we already taken into account in the sample size calculations a 10% drop-out.

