## **6.6 Follow-up of subjects withdrawn from treatment**

N/A

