#### *Conduct consent*

We use the deferred consent concept for participation. In this cluster randomized trial, the compared groups both consist of standard care (i.e. NVK guideline or EOS calculator, see chapter 3 and 6.2). Consent for standard care is not required. Consent for data collection of standard care and completing a questionnaire will be gained by the investigator/research nurse. Most of the time this will be within the first 24 hours after birth. We may gain consent in a later phase (more than 24 hours after birth), since we think it is reasonable and achievable to gain consent during normal working hours. No data will be collected from patients who refuse to participate.

There are two consent forms: one for permission to use data of the child, which has to be signed by both parents or guardians, and one for permission to use data of the mother, which has to be signed by the mother only. The consent forms consist of two pages. The first page contains general statements and specific statements about participating in the

study. On this page parents or guardians will be asked to give consent to collect data from the electronic medical records of mother and child (see chapter 3 and the patient information form), and to fill in one questionnaire about quality of life on day 14. Signing the form by (both) parent(s)/guardian(s) automatically means that they agree with these statements. There are three optional statements included on the first page, where they can choose whether they give permission. Parent(s)/Guardian(s) will be asked whether they give permission to save personal data from mother and child for a longer period to use these for future research, and to possible study-related follow-up (questionnaires) in the future (after day 14).

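### Section 6.4 lets an unblinded investigator withdraw a newborn from a data-only study for a medical reason that overlaps the safety composite, and no section secures that newborn's co-primary data

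*Protocol*

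**What the plan says.** Section 6.4 first gives subjects the right to leave at any time, then adds: "The investigator can decide to withdraw a subject from the study for urgent medical reasons". The exit is from the study, not from a treatment.

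Section 6.5 covers what follows: "Subjects will not be replaced after withdrawal because we already taken into account in the sample size calculations a 10% drop-out". Section 4.4 makes the same allowance: "The potential drop-out or withdrawal is estimated at 10" per cent. Section 6.6 is headed "Follow-up of subjects withdrawn from treatment" and its whole content is N/A.

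On what participation means, section 6.2 says of the assigned protocol as standard care: "This is independent of participating in this study". Section 9.2, under Conduct consent, says: "Consent for data collection of standard care and completing a questionnaire will be gained by the investigator/research nurse". Sections 3 and 6.2 add that physicians may always depart from the assigned protocol; such departures are recorded.

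The safety co-primary in section 6.1.1 is "A composite non-inferiority outcome regarding the presence of one or more of the following four predefined safety criteria": respiratory support, a fluid bolus for instability due to sepsis, NICU referral for sepsis treatment, or proven EOS. On the analysis set, section 4.4 says: "All participants taking part in the study will be analyzed according to the ITT principle".

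**The concern.** A clause of this kind makes sense where leaving the study takes a patient off a study treatment. Here there is no individual study treatment. Leaving the study changes nothing at the bedside, so an investigator's medical withdrawal can only affect whether data are collected.

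The trigger is also related to the outcome. Newborns with an urgent medical reason will largely be those who have, or are about to have, a component of the composite. The person who decides knows the arm, since section 6.2 leaves hospitals and physicians unblinded and section 6.1.1 concedes that unconscious bias is possible.

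At stake is the co-primary that must show the calculator is safe. In a non-inferiority comparison, losing events from the experimental arm favours the claim. An SAP can say how withdrawn newborns are analysed, but it cannot recover outcomes that sites were allowed to stop collecting.

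**Working it through.** **1. What a medical withdrawal can change.**
- Care: nothing. The assigned protocol applies to every at-risk newborn in the hospital (sections 3, 6.2, 9.2), and departing from it does not require leaving the study.
- Data: record abstraction and the questionnaire (section 9.2). These are all that consent covers.

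**2. The protocol's own sample size (section 4.4).** Inputs: 10% in both arms, absolute margin 5%, 80% power, one-sided alpha 0.025, ICC 0.0025, 10 hospitals.
- Unclustered: (1.96 + 0.842)² × 2 × 0.10 × 0.90 / 0.05² gives 566 per arm.
- Design effect at 164 per cluster: 1 + 163 × 0.0025 = 1.4075. Total 2 × 566 × 1.4075 = 1593, which is 2.8% below the stated 1640, so the figure is reproduced closely.
- Drop-out: 1640 / 0.9 = 1823, rounded up to 183 per cluster, gives 1830.

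The drop-out allowance is 915 − 820 = 95 newborns per arm. Expected composite events are 0.10 × 820 = 82 per arm. A loss of events of any plausible size would therefore fit inside the planned drop-out and would not stand out as unusual attrition.

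**3. Illustration of the effect on the non-inferiority claim.** The protocol gives no expected number of such withdrawals, so the fractions below are assumptions.
- 915 per arm; design effect 1 + 182 × 0.0025 = 1.455; effective size 915 / 1.455 = 629 per arm.
- True rates 10% control and 15% calculator, so the true relative risk sits exactly at the 1.5 limit of section 8.1.
- If a fraction f of newborns with events is removed, the observed rate is r = p(1 − f) / (1 − pf), and the arm shrinks by the factor (1 − pf).
- SE of log RR = √[(1 − r₁)/(r₁n₁) + (1 − r₀)/(r₀n₀)].
- Chance of claiming non-inferiority = Φ[(ln 1.5 − ln RR)/SE − 1.96].

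Worked case, 10% of calculator-arm events lost and none in control: 0.10 × 0.15 × 915 = 13.7, about 14 newborns or 1.5% of the arm. r₁ = 0.135 / 0.985 = 0.1371; RR = 1.37; n₁ = 629 × 0.985 = 619; SE = 0.156; (0.4055 − 0.3153) / 0.156 = 0.58; Φ(0.58 − 1.96) = 8.3%.

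| Events lost, calculator / control | Observed RR | False non-inferiority claim |
|---|---|---|
| 0 / 0 | 1.50 | 2.5% |
| 10% / 0 | 1.37 | 8.3% |
| 20% / 0 | 1.24 | 22% |
| 20% / 10% | 1.36 | 8.5% |
| 20% / 20% | 1.52 | 2.2% |

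With 820 analysed per arm and a design effect of 1.4075, losing 10 calculator-arm events gives 6.5% and losing 20 gives 15%, which is the same pattern.

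**4. Which losses the text allows.** The formula removes the newborn altogether. That covers two cases: a newborn withdrawn before any component has occurred, whose later event goes uncollected, and a newborn withdrawn after an event and then dropped from the analysis. The protocol is silent on both.

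**The case against.** Three stronger readings are tempting, and the protocol does not support them.

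A reader might infer that the protocol rules out follow-up after such a withdrawal, because section 6.6 says N/A. Its heading concerns withdrawal from treatment, and in a trial without individual treatment N/A is a fair entry. For withdrawal from the study the protocol is silent.

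A reader might infer a contradiction with the ITT sentence in section 4.4. That sentence does not exclude withdrawn newborns, and a drop-out allowance beside an ITT analysis is ordinary planning. The ITT statement is left unsecured, not contradicted.

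A reader might take the 8% or 22% as the expected bias. Each driver is assumed: a true relative risk at the limit, the fraction withdrawn, and the difference between arms. Nothing in the protocol says the clause will be used more in calculator hospitals. Because withdrawal does nothing for the newborn's care, investigators may have little reason to use it at all.

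The protocol also guards the data in part. Section 3 says data are collected and used when physicians depart from the assigned protocol. Section 6.3 has NICU referral and NICU data recorded. Section 7.2.2 puts NICU referral in the eCRF because it is a non-inferiority criterion. Section 7.4 follows adverse events until they resolve or stabilise. A newborn withdrawn because of a composite event has already met the binary endpoint, and no section orders recorded data deleted. The bar on data collection in section 9.2 concerns families who refuse.

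These points narrow the concern but do not remove it. None of the safeguards is said to apply after withdrawal from the study. Adverse event follow-up is not endpoint collection: section 7.2.2 exempts several kinds of NICU referral, and antibiotic starts for EOS within 72 hours, from its seriousness criteria.

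**Conclusion.** The point holds in a limited form. Section 6.4 creates an exit that has no protective purpose in a data-only study, is decided by someone who knows the arm, and is triggered by conditions that overlap the safety composite. Sections 4.4 and 6.5 plan for those newborns as drop-out, and no section says their co-primary data are kept or collected.

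The direction of bias is conditional: towards non-inferiority if the clause is used more in calculator hospitals, about none if it is used equally, although events are then discarded. The size cannot be derived from the protocol. The rise from 2.5% to about 8% is an illustration under the stated assumptions. The sample size arithmetic is not affected. Severity is minor to moderate: the existing safeguards and the likely rarity of use keep it from being a must-fix.

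**What to change.** Delete the investigator-withdrawal sentence in section 6.4, so that only parents or guardians can end participation. Alternatively, keep it and state in sections 6.4 and 6.6 that:

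- clinical deterioration, transfer or a change of management does not end participation;
- such newborns remain in the ITT set;
- antibiotic start and all four composite components are collected from the record to the end of follow-up, unless parents withdraw consent for data use.

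Reporting withdrawals by arm and any sensitivity analysis for them can be left to the SAP. The cost is a wording amendment and a little more record abstraction, with no extra newborns, visits or procedures and no change to clinical care.

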## **6.5 Replacement of individual subjects after withdrawal**

Subjects will not be replaced after withdrawal because we already taken into account in the sample size calculations a 10% drop-out.

## **6.6 Follow-up of subjects withdrawn from treatment**

N/A

### **6.6.1 Premature termination of the study**

Interim analyses for safety are planned after outcome data for the first 200 participants in either arm (in total 400) have come available. This will be repeated at a total of 900 participants. Based on the results of the safety interim analysis the DSMB may advise to stop the trial. The sponsor will inform the accredited METC in case of termination and the reason for it within 15 days.

## 7. SAFETY REPORTING

### 7.1 Temporary halt for reasons of subject safety

In accordance with section 10, subsection 4, of the WMO, the sponsor will suspend the study if there is sufficient ground that the continuation of the study will jeopardize the subject health or safety. The sponsor will notify the accredited METC without undue delay of a temporary halt including the reason for such an action. The study will be suspended pending a further positive decision by the accredited METC. The investigator will take care that all subjects are kept informed.

### 7.2 AEs and SAEs

All (serious) adverse events reported spontaneously by the parent(s)/guardian(s) of the subject or observed by the investigator, or his staff will be recorded up until and including day 14 after birth. This period is consistent with the follow-up time and reasonably includes complications that may be linked to initial EOS management, such as a different course of EOS or readmission. In the unusual case that a newborn still receives antibiotic therapy after day 14 of life because of EOS (or a SAE), (serious) adverse events will be reported until the end of therapy.

#### 7.2.1 Adverse events (AEs)

Adverse events are defined as any undesirable experience, symptom, or medical condition occurring to a subject during the study, whether or not considered related to the trial procedure.

Not considered AEs are:

- regurgitation;
- colic;
- abnormal laboratory values, not related to neonatal early-onset infection, unless they are considered clinically significant or require therapy (except phototherapy for hyperbilirubinemia, and ferrous fumarate or erythrocyte transfusions for anemia);
- abnormal test results, other than blood cultures, unless they are considered clinically significant or require therapy.

### 7.2.2 Serious adverse events (SAEs)

A serious adverse event is any untoward medical occurrence or effect that

- results in death;
- is life threatening (at the time of the event);
  - o except, if it concerns neonatal (advanced) life support directly after birth;
  - o except if it concerns surfactant therapy;
  - o except referral to a NICU:
    - (need for mechanical ventilation because of) surfactant therapy;
    - insertion of central venous lines;
    - respiratory support for prematurity.
- requires hospitalization or prolongation of existing inpatients' hospitalization;
  - o unless a newborn will start with antibiotic therapy for (suspected) EOS during the observation period or after discharge, but within 72 hours after birth. See also 5.4.;
  - o unless it is due to prematurity.
- results in persistent or significant disability or incapacity; or
- any other important medical event that did not result in any of the outcomes listed above due to medical or surgical intervention but could have been based upon appropriate judgement by the investigator.

Referral to a NICU will be included in the electronic Case Report Form (eCRF), since this is one of the non-inferiority criteria.

Each study site will report all SAEs to the coordinating investigators within 24 hours after becoming aware of the event. The coordinating investigators will report all SAEs to the sponsor without undue delay after obtaining knowledge of the events. The sponsor will report the SAEs through the web portal *ToetsingOnline* to the accredited METC that approved the protocol, within 7 days of first knowledge for SAEs that result in death or are life threatening followed by a period of a maximum of 8 days to complete the initial preliminary report. All other SAEs will be reported within 15 days after the sponsor has first knowledge of the serious adverse events.

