For the Dutch situation, equipoise between the current guideline and the EOS calculator can be established given balance of risk for both over- and undertreatment of EOS for both strategies: the current guideline is likely to result in more overtreatment with adverse consequences, but potentially carries a smaller risk for treatment delay (although it is unclear to what clinical significance). A large body of evidence now supports the safety of the EOS calculator approach, but validation outside of the North-American setting is limited, especially for safety outcomes. Equipoise between both strategies is confirmed by the recently updated version of the NICE guideline (the NVK guideline was based on the 2012 version), which includes use of the ‘EOS calculator’, as a valid alternative approach to allocate antibiotics to newborns.(19) Equipoise can also be inferred from recommendations of the American Academy of Pediatrics, which considers both a risk-factor based approach and the EOS calculator as valid strategies. We compared the EOS calculator to the NVK guideline in a post-hoc analysis of our multicenter study (20), and found that the EOS calculator recommended significantly fewer antibiotics than the NVK guideline. This result is in line with the results of previous international research showing that the EOS calculator is proven to be effective and safe for reducing antibiotic overtreatment (17,21).

A prospective cluster-randomized Dutch validation study of the EOS calculator is needed before complete adoption of the EOS calculator, because of the following reasons:

1) Multicenter validation of actual EOS calculator use has not been performed in the Netherlands.

2) To date, no randomized prospective study of EOS calculator use with safety as an outcome measure has been performed. Specifically, there are no studies that take into account the potential effects of a treatment delay due to EOS calculator use. This especially holds true for cases that are clinically suspect for EOS, but not culture-confirmed. The study here proposed by us is, to the best of our knowledge, the first.

This protocol describes a cluster-randomized trial, which is the logical next step to our previous research (18,22–28). The study aims to investigate whether the use of the EOS calculator safely reduces antibiotic exposure in newborns with suspected EOS compared to the current Dutch guideline.

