### 7.5 Data Safety Monitoring Board (DSMB) / Safety Committee

An independent DSMB will monitor this trial and consists of several members with expertise in the relevant fields of paediatrics, epidemiology and statistics. The composition of the DSMB is outlined in the DSMB Charter. This document also includes statements regarding conflict of interest by the members of the board and an outline of tasks and responsibilities.

The safety of trial participants is of primary concern for the DSMB. The DSMB will meet to discuss the safety review after the outcome data of the first 400 patients (200 in the control arms and 200 in the intervention arm) and 900 patients have become available. Additional reviews will be conducted at the DSMBs request. The DSMB can advise to terminate the study prematurely in case an interim analysis shows clear harm of either one of the interventions or due to external evidence. A formal interim analysis for efficacy (inferential testing) will not be conducted. The DSMB will not be blinded when first assessing the data.

Criteria on which the DSMB may decide to terminate the trial are described in the DSMB charter (see 'K5. DSMB Charter'). The advice(s) of the DSMB will be sent to the principal investigator and the trial methodologist. Should the principal investigator decide not to fully implement the advice of the DSMB, the principal investigator will send the advice to the reviewing METC, including a note to substantiate why (part of) the advice of the DSMB will not be followed.

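### Section 7.2.2 exempts hospitalisation for antibiotics first started within 72 hours from SAE status on that criterion, even when EOS is culture-proven

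*Protocol*

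**What the plan says.** Protocol section 7.2.2 lists five criteria that make an event serious: death, threat to life, hospitalisation or prolonged stay, disability, and a residual class of important medical events. The third, "requires hospitalization or prolongation of existing inpatients' hospitalization", carries an exception: "unless a newborn will start with antibiotic therapy for (suspected) EOS during the observation period or after discharge, but within 72 hours after birth". The clause refers the reader to section 5.4, which explains that a missed case is one in which antibiotics were not started immediately after birth, and that the calculator strategy leans on observation.

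Expedited reporting is tied to SAE status. "Each study site will report all SAEs to the coordinating investigators within 24 hours" of becoming aware of them. The sponsor then reports to the ethics committee within 7 days (fatal or life-threatening) or 15 days (all others).

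Section 7.2 records adverse and serious adverse events through day 14 and defends that window because it "reasonably includes complications that may be linked to initial EOS management, such as a different course of EOS or readmission". Section 1 gives, among its reasons for the trial, that "there are no studies that take into account the potential effects of a treatment delay due to EOS calculator use".

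On oversight, section 7.5 says: "The DSMB will meet to discuss the safety review after the outcome data of the first 400 patients", and again after 900. Section 8.3 makes these reviews descriptive.

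**The concern.** A newborn whose antibiotics start late because the first advice was to observe is the safety event that most directly bears on treatment delay. Exempting late starts for suspected EOS that later proves culture-negative is reasonable. They are expected under both strategies, and reporting each one would swamp the system. But the clause draws no line between those and culture-proven infection. A proven case that was not treated at first, and is serious only because the child was readmitted or kept longer, falls under the same exception.

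At stake is the speed and visibility of oversight. Such a case would be recorded, but with no 24-hour report from the site and no 15-day report to the ethics committee. It would also be absent from the SAE list in the annual safety report (section 7.3), although that report also contains a safety analysis.

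**Working it through.** No statistical formula governs the scope of an SAE definition, so the check is mainly a reading of the text. A short calculation then sizes it.

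**Step 1: apply the five criteria to a test case.** Take a newborn in either arm who is observed without antibiotics, goes home, and is readmitted at 50 hours. The child is clinically stable and treated, and the blood culture grows a pathogen.

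- Death: not met.
- Life-threatening: not met, as the child is stable.
- Hospitalisation: met on its face, then removed by the exception. Antibiotics started after discharge and within 72 hours.
- Disability: not met.
- Residual class: available only by investigator judgement. It is worded for "any other important medical event that did not result in any of the outcomes listed above". Since hospitalisation did occur here, the fit is uncertain, and nothing requires its use.

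The case can therefore pass without an SAE report.

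**Step 2: see how far the 72-hour limit narrows this.** Section 6.1.1 defines proven EOS by a culture taken within 72 hours of birth, and section 6.3 has the culture taken before antibiotics start. If treatment follows soon after the culture, most late-treated proven cases fall inside the exempt window.

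**Step 3: list the other routes by which the case is seen.**

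- Adverse-event recording to day 14. Section 7.2.1 does not exclude blood culture results.
- Readmission data for newborns without antibiotic therapy (section 6.3).
- The safety composite (section 6.1.1). It counts proven EOS however promptly treated, and does not itself count late start or readmission.
- The secondary endpoint on antibiotic starts, limited to symptom onset at 24 to 72 hours (section 6.1.2).
- The DSMB reviews. Outcome data from the remaining 1830 − 900 = 930 participants (930/1830 = 50.8%) fall under no further scheduled review, though the DSMB may ask for more.

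None of these has a reporting clock for the single case.

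**Step 4: size.** Inputs are 1830 participants, 915 per arm (section 4.4); 20% of births with suspected EOS (section 4.1); proven EOS at 0.5 to 2.0 per 1000 live births (section 1); and missed shares of 5/18 with the calculator and 8/28 with conventional care (section 5.4). The two shares reproduce as 27.8% and 28.6%, matching the stated 28% and 29%.

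- Births represented: 1830 / 0.20 = 9150.
- Proven EOS: 9150 × 0.0005 = 4.6, to 9150 × 0.002 = 18.3.
- Missed, both arms, at 5/18: 1.3 to 5.1.
- By arm (915 / 0.20 = 4575 births; 2.3 to 9.15 proven cases): calculator at 5/18, 0.6 to 2.5; control at 8/28, 0.7 to 2.6.

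For scale, the composite at its expected 10% gives 183 events. The missed proven cases would be 1.3/183 = 0.7% to 5.1/183 = 2.8% of them, so composite totals alone would not make them visible.

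**The case against.** The strongest reply is that the exception is deliberate. It cites section 5.4, and handling expected, endpoint-like events outside expedited reporting is an accepted design choice. The events are still recorded and reviewed. This stands for suspected EOS. It is weaker for proven EOS, because the cited justification rests on small counts from before-after studies, while section 1 says the effects of delay have not been studied.

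A reader might infer several stronger things that the protocol does not support:

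- **That delayed treatment never triggers an expedited report.** The exception sits under one criterion of five and ends at 72 hours. Fatal, life-threatening, disabling and judged-important cases remain SAEs, as does hospitalisation for treatment first started after 72 hours.
- **That sections 7.2 and 7.2.2 flatly contradict each other.** Section 7.2 sets a recording window for all adverse events, and an exempt case can still be recorded as one. The two sit awkwardly together.
- **That the DSMB is not told.** Section 7.2.2 shows no route to it, but the DSMB Charter, where tasks and stopping criteria are placed, is not available here and may supply one.
- **That the exposure is specific to calculator hospitals.** The 1 to 5 cases span both arms, with nearly equal missed shares.
- **That the central-line exception for NICU referral hides sepsis referrals.** Nothing says a referral for sepsis would be classed there, and all NICU referrals go into the eCRF.

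**Conclusion.** The point holds in a limited form. Hospitalisation or a prolonged stay for antibiotics first started within 72 hours is not an SAE on that criterion, even with culture-proven EOS. If no other criterion is met, the case reaches reviewers only through recorded data and the descriptive DSMB reviews. It is a gap in the wording of the safety reporting and leaves the trial's estimates and error rates unaffected.

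The expected number is small: about 1 to 5 cases across both arms, of which about 0.6 to 2.5 are in the calculator arm. This assumes that all EOS arises in at-risk newborns, that consent is unrelated to EOS, and that the section 5.4 shares, based on 18 and 28 cases, carry over. If some EOS arises in newborns without a risk factor or sign, both ends fall. Some of these cases would be SAEs on another criterion anyway, so the number actually exempt may be lower.

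**What to change.** Reconcile sections 7.2 and 7.2.2 by limiting the exception to antibiotic starts for EOS that is suspected but not proven, using the section 6.1.1 definition of proven EOS. Proven EOS in a newborn not treated initially, or readmitted, would then be an SAE on the existing 24-hour site clock, applied identically in both arms. That clock already runs from the site becoming aware, so it can start when the culture result arrives. Add that these reports are forwarded to the DSMB as they come in, unless the Charter already provides for it.

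The change need not extend to every late start followed by respiratory support. Section 6.1.1 counts low-flow oxygen in the first week as such support, and late start is undefined, so that rule could generate many uninformative reports.

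The cost is a wording change to the protocol and the reporting form, plus about 1 to 5 extra reports over the whole trial. Treatment, sample size and analysis are unchanged.
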